## Methods

### Study Design

We will use collected data from a randomized controlled trial (RCT; N=300) of internet-delivered CBT for patients diagnosed with AD or ED compared to an active, internet-delivered control condition consisting of general health-promoting advice. A priori power analysis conducted for the main outcome in the RCT indicated that 300 study participants would be needed for a 90% power to detect a between-group effect size of Cohen *d*=0.4 with a significance level of .05 and an expected attrition rate of 10%. Due to the limited sample size and general lack of knowledge on predictors of treatment effect, prediction models in this study will be based on pooled data from both treatment arms. The study design is prospective, and predictors will include sociodemographic and clinical information, clinician-assessed data, self-rated symptoms, and results from cognitive test scores. The results will be reported in line with the TRIPOD+AI (Transparent Reporting of a Multivariable Prediction Model for Individual Prognosis or Diagnosis+Artificial Intelligence) statement [30].

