### Procedure

#### Participants

In total, 300 nationally recruited individuals were diagnosed with a primary diagnosis of AD (n=142, 47.3%) or ED (n=158, 52.7%) and were included in the RCT. Participant recruitment was carried out through social media, newspaper advertisements, and information provided to health care clinics. Participants self-referred to the study web page, where they signed digital informed consent and completed a screening battery consisting of sociodemographic and clinical background questions as well as self-report symptom questionnaires. Participants were subsequently clinically assessed by a psychologist using a structured diagnostic interview, including Mini International Neuropsychiatric Interview [31], self-rated ED [32], and the Adjustment Disorder New Module-8 (ADNM-8) [33]. For inclusion, participants needed to (1) fulfill the criteria for a primary diagnosis of AD or ED, (2) be aged between 18 and 65 years, (3) have regular access to a computer with internet access, and (4) be able to read and write in the Swedish language. Exclusion criteria included (1) drug use or addiction during the past 6 months, (2) current or past psychosis or bipolar disorder, (3) current risk of suicide, (4) changed psychopharmacological treatment in the past month, (5) other ongoing psychological treatment, and (6) previous experience of CBT for AD or ED in the past year.

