#### Data Cleaning and Preparation

We will transform categorical variables into a format suitable for numerical analysis. For binary categorical variables, we will use label encoding. For multinomial variables, we will apply one-hot encoding. In addition, for ordinal data, which have a natural order, we will transform the categories into integers.

Predictor variables with over 20% missing data will be excluded from the analysis. Categorical variables exhibiting low variance, as determined by predictors with <5% of a certain response will be removed. For instance, by removing the variable “Sleep medication” if it only occurs in 3 out of 300 patients. This approach aims to reduce unnecessary complexity in the predictions and to minimize the risk of overfitting. To control for multicollinearity, variables with a correlation coefficient ≥0.8 will be removed from the traditional prediction analysis but will be retained for the ML model development. Data that are highly skewed will be transformed if deemed appropriate.

Cognitive test results will be manually reviewed before model fitting to validate a proper result. Comments pertaining to technical difficulties and disturbances that may have affected the test result will be assessed by two of the authors and lead to exclusion if so judged. Participants who have noted during screening that Swedish is not their native language will be excluded from the analysis for CERAD and FAS. We will standardize the raw scores from the cognitive tests using normative regression models with age, education and sex as covariates. This standardization process will convert raw scores into *Z* scores, as previously described by Franke Foyen et al [62] and for a full overview of the multiple linear regression models used and how they were calculated, see the studies by Mindmore [77] and van den Hurk et al [78].

Patients who have missing data for the posttreatment PSS-10, ie, the missing outcome variable for the primary aim, will be replaced by a PSS-10 process measurement at week 10 if available; If not, the patient will be excluded from the analysis. The number of participants excluded from the final models will be described.

To prepare our primary outcome, RCI for the PSS-10 before to after treatment will be computed using the following formula [39]:

Cronbach α=0.83 from normative data will be used [38]. Patients exhibiting an RCI of −1.96 will be classified as responders.

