#### Train Test Split

As the ultimate goal of any model is to predict an outcome in unseen data, the ML models will be developed using a training set, and then evaluated on a test set stratified on main diagnosis (AD or ED) and responder status. In total, 70% of the data will be used for selecting predictor variables and training the models, and 30% for testing the prediction accuracy of the models. The choice of 70 to 30 was due to the limited size of our sample, as fewer observations in the testing data makes it difficult to use uncommon predictors. No external validation set is currently available at the time of writing.

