#### Model Descriptions

We will train and evaluate 4 different ML classifiers, a multiple logistic regression (LogReg) classifier using elastic net, a random forest (RF) classifier, a support vector machine (SVM) classifier, and an AdaBoost classifier. For a review of the models used, see the textbook by Geron [79]. In short, the LogReg classifier works by modeling the probability of a binary outcome based on one or more predictor variables, using the logistic function to ensure the output is between 0 and 1. We will use elastic net regularization to facilitate feature selection and prevent overfitting. Elastic net combines L1 (lasso) and L2 (ridge) penalties, encouraging sparsity and maintaining stability in the model. The RF classifier works by building multiple decision trees on random subsets of data and predictors. Each tree’s prediction is based on splits that minimize variance in the target variable, with the final model ensembling these predictions. The SVM classifier works by finding the hyperplane that maximizes the margin between different classes in the feature space. SVM is particularly effective in high-dimensional spaces and when the number of dimensions exceeds the number of samples. AdaBoost, the final classifier, works by combining multiple weak classifiers, typically decision trees, into a single strong classifier. It sequentially fits these weak learners on repeatedly modified versions of the data, focusing more on misclassified instances to improve overall accuracy.

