#### Model Interpretation

The models developed to identify the responder status will be evaluated using BACC, precision and recall, both in the training set obtained through k-fold cross-validation and in the test set. Predictor importance in the RF model will be determined using Scikit-learn’s Feature importance function, which quantifies each predictor’s contribution to the model’s balanced classification accuracy. Area under the curve will be used to assess the models’ capability to distinguish between classes accurately. The approach will aim to provide a clear understanding of the models’ effectiveness and the role of various predictors. Our primary outcome of interest for comparison will be BACC in each model in the test set with the aim that (1) the model should perform better than a dummy model that simply predicts the most common responder status, and (2) that the model should perform 67% BACC or above to be deemed clinically useful [28]. Furthermore, the models will be statistically compared using bootstrap sampling. Specifically, we will generate 5000 bootstrap samples from the test set, calculating the BACC for each model on each sample. The distributions of these bootstrap BACCs will be compared and we will conclude that there is a statistically significant difference between models if the CIs do not overlap.

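### Calling two classifiers different only when their separate bootstrap CIs do not overlap is far stricter than a 5% test, because all are scored on the same test patients

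*Protocol article*

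**What the plan says.** Four classifiers are developed (Model Descriptions: "We will train and evaluate 4 different ML classifiers") on 70% of the data and evaluated on one held-out set, with "30% for testing the prediction accuracy of the models" (Train Test Split). The trial enrolled 300 patients (Participants). Those with neither a post-treatment nor a week-10 PSS-10 are dropped (Data Cleaning and Preparation: "If not, the patient will be excluded from the analysis").

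Model Interpretation sets two aims for test-set BACC: each model should beat a majority-class dummy, and "the model should perform 67% BACC or above to be deemed clinically useful". It then adds a statistical comparison between models: "we will generate 5000 bootstrap samples from the test set, calculating the BACC for each model on each sample". The decision rule is: "we will conclude that there is a statistically significant difference between models if the CIs do not overlap". The article gives no confidence level, error rate or power for this comparison, and no adjustment for the number of pairs.

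**The concern.** Two estimates can differ significantly at the 5% level while their separate 95% intervals overlap. Requiring non-overlap is therefore a stricter test than 5% even for independent estimates. Here the estimates are not independent. All four classifiers are judged on the same patients, and patients who are hard for one model tend to be hard for the others. Positive correlation makes the difference more precise than the separate intervals suggest, so the rule becomes stricter still. The planned bootstrap yields exactly the paired draws needed for a valid comparison, and the rule then leaves the pairing unused.

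At stake is how the classifier comparison is read. The Discussion presents comparison between methodological approaches as one purpose of the study. A non-significant result that comes mostly from the rule invites the reading that the classifiers perform alike.

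**Working it through.** **Stated design figure.** The only stated power calculation is for the trial's main outcome (Study Design: d = 0.4, 90% power, level .05, 10% attrition, N = 300). Taken as two-sided, n per arm = 2 × (1.960 + 1.282)² / 0.4² = 131.3, so 132. The total is 264, and 264 / 0.9 = 293.3, so 294, close to 300. It reproduces, but it does not address the classifier comparison.

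**Inputs from the article.** Test share 30%; at most 300 patients; four classifiers, so 6 pairs; reference BACC 0.67.

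**Assumptions, not in the article.**
- CIs are 95%.
- The test set is 81 (10% without an outcome: 270 × 0.3) to 90 (300 × 0.3).
- Responders are 40%, that is 32 of 81 or 36 of 90.
- The correlation ρ between two models' BACCs is 0 to 0.7.
- Standard errors are equal and the normal approximation holds.

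**Step 1: standard error of one BACC.**
SE = 0.5 × √[0.67 × 0.33 × (1/n_resp + 1/n_nonresp)]
- n = 81: 0.5 × √[0.2211 × (1/32 + 1/49)] = 0.0534
- n = 90: 0.5 × √[0.2211 × (1/36 + 1/54)] = 0.0506

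**Step 2: observed gap needed.** Non-overlap requires |difference| > 2 × 1.96 × SE, which is 0.198 (n = 90) to 0.209 (n = 81), or about 20 to 21 points. The distance from chance (50%) to the 67% benchmark is 17 points, so a classifier observed at 67% would not be called different from another classifier observed at 50%.

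**Step 3: actual level.** SD(difference) = SE × √[2(1 − ρ)]. The rule therefore requires |z| > 2 × 1.96 / √[2(1 − ρ)], and the two-sided level follows:

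| ρ | z required | level per pair |
|---|---|---|
| 0 | 2.77 | 0.56% |
| 0.3 | 3.31 | 0.09% |
| 0.5 | 3.92 | 0.009% |
| 0.7 | 5.06 | below 0.0001% |

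**Step 4: power for a true 10-point gap.** Power = Φ(0.10/SD − z) + Φ(−0.10/SD − z), with z from Step 3 for the stated rule, 1.96 for an unadjusted paired test, and 2.638 for the strictest Holm step (0.05/6 = 0.0083). Ranges run from n = 81 to n = 90:

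| ρ | non-overlap rule | paired, unadjusted | paired, strictest Holm step |
|---|---|---|---|
| 0 | 7–9% | 26–29% | 9–11% |
| 0.3 | 4–5% | 35–39% | 15–17% |
| 0.5 | 2–3% | 47–51% | 22–25% |
| 0.7 | under 1% | 68–72% | 41–47% |

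**Step 5: larger gaps.** Over the same range of ρ, the non-overlap rule has about 41–52% power at 20 points and 70–91% at 25 points.

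**Step 6: check by simulation.** Correlated correct/incorrect calls were simulated, with percentile bootstrap intervals. Type I error of the non-overlap rule was 0.5–0.7%, 0.1–0.2% and 0.0% at BACC correlations of 0, about 0.3 and about 0.6. The paired interval gave about 5–7%.

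**Step 7: dummy model.** A majority-class dummy has BACC exactly 0.50 with no spread. Non-overlap then reduces to asking whether the classifier's own CI excludes 0.50, an ordinary test. Its power at true BACC 0.67 is Φ(0.17/SE − 1.96), or 89–92%.

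**The case against.** **The rule errs on the safe side.** It will not create false claims that one classifier is superior. With six pairs, a Bonferroni level of 0.83% is not far from 0.56%. This stands only at zero correlation. The article does not give multiplicity as a reason, and the rule's level falls with a correlation that nobody controls.

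**The CI level is not stated.** A lower level would loosen the rule, so 95% is an assumption. But no single level repairs it: about 83% intervals would give 5% at ρ = 0, and about 67% intervals at ρ = 0.5.

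**The small test set explains much of the low power.** This stands. Even the unadjusted paired test has only about 10–17% power for a 5-point gap at correlations up to 0.5, and Holm adjustment takes back part of the gain. At ρ = 0 the strictest Holm step (9–11%) barely improves on the stated rule (7–9%).

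**Stronger readings that a reader might infer.** One is that the comparison must end in no significant difference whatever the truth. Step 5 shows otherwise for gaps of 20 points and above. Another is that the study's main conclusions are compromised. They are not: the stated hypotheses are to beat the dummy and to reach 67%, and neither depends on comparing two variable intervals. The article nowhere hypothesises that one classifier beats another.

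**Conclusion.** The rule is wrong as written, and nothing elsewhere in the article repairs it. If the CIs are 95%, it operates at 0.56% or less per pair rather than 5%. The loss of power falls mainly on gaps well below 20 points. The figures rest on the assumed CI level, 40% responders, the assumed correlations and 81 to 90 test patients. The direction of the error does not depend on the exact values: with 95% CIs the rule is stricter than 5% at every correlation from 0 upwards.

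Because the flaw is conservative and confined to a secondary comparison among the four classifiers, it should be fixed but does not threaten the primary aims.

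**What to change.** Replace the closing sentence of Model Interpretation with, for example:

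> For each of the 6 pairs of classifiers we will compute the difference in BACC within each of the 5000 bootstrap samples and report its 95% percentile interval. A two-sided bootstrap p-value will be derived from the distribution of each paired difference and Holm-adjusted over the 6 pairs; two classifiers will be called different if the adjusted p-value is below .05. Each classifier will be compared with the dummy by whether its own 95% CI excludes 0.50.

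Add that a non-significant result is not evidence of equal performance, and let the reported intervals show how large a difference remains possible.

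The cost is a few lines of code on the same bootstrap samples. The article says the data had not been analysed for this study as of March 2025. If that is still so, the rule can be changed before any result is known.

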**Figure 1 figure1:**
[figure not shown]
CONSORT (Consolidated Standards of Reporting Trials) diagram showing participant flow through enrollment, allocation, follow-up, and analysis. CBT: cognitive behavioral therapy.

A cross-sectional study investigating baseline cognitive functioning as compared with a healthy reference group has been published indicating small-to-moderate objective cognitive impairments [62], raising the question of whether objective cognitive function serves as a predictor of treatment response. In addition, an interim analysis of pre- and postcomparisons was presented at a conference in September 2022. These earlier analyses addressed separate research questions and did not influence the design, methods, or objectives of the current protocol. As of March 2025, data have not been analyzed for this study.

## Discussion

### Overview

This study will use a high-quality dataset from an RCT to investigate potential treatment predictors using both traditional prediction methods and an ML paradigm. This dual approach will enable the identification of predictors of treatment response in a patient population where prior research is limited. In addition, it will facilitate comparisons between different methodological approaches to prediction research.

### Comparison to Prior Work

To the best of our knowledge, this is the first study to apply an ML approach to study predictors of treatment outcome in patients diagnosed with AD or ED. In line with previous traditional prediction research of treatment outcomes in stress-related disorders, we hypothesize that younger age, education level, symptom severity, treatment credibility, and history of sickness absence will predict treatment response [15,22]. Furthermore, we anticipate that the ML models will outperform a dummy model and achieve a BACC of 67% or higher, surpassing the benchmark indicated by Forsell and others [28]. If confirmed, our findings would support the notion that predictive models using sociodemographic, clinical, self-rated, treatment-related, and potentially cognitive variables are valuable when predicting therapy outcomes, as have been suggested in other patient populations [17,18,80]. In subsequent research, these models should be externally validated and tested in implementation trials to assess their utility as decision support tools. Such trials could evaluate whether integrating predictions into treatment planning improves outcomes and supports personalized care.

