### Outcomes

The primary outcome in this study and the original RCT is PSS-10 [35]. The PSS-10 is a self-report questionnaire developed to evaluate an individual’s perception of life as unpredictable, uncontrollable, and overwhelming. Responses are recorded on an ordinal scale ranging from 0 n*ever* to 4 *very often*, reflecting the individual’s feelings and thoughts over the past month. It contains statements, such as ‘*In the last month, how often have you been upset because of something that happened unexpectedly?’* and sum scores range from 0 to 40. The PSS is the most commonly used outcome measure of stress-management interventions globally [8,36,37]. For this study, a Swedish version of the PSS-10 was used. The PSS-10 has been found to exhibit high internal consistency (Cronbach α=0.84) and adequate construct validity [38]. The PSS-10 was administered digitally through the web-based study platform before randomization to treatment, every 3 weeks during the treatment phase, and at treatment completion (12 weeks). During treatment, the instructions for the PSS-10 were modified to have patients consider the last week instead of the last month. For this study, the sum score of the PSS-10 will be dichotomized into responder or nonresponder after treatment based on the RCI criteria [39] to differentiate between statistically significant change and those attributable to measurement error or natural variability. The PSS-10 baseline and 3-week measurement will also be used as predictors.

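### Meeting the dummy and 67% aims cannot show that predictors other than the PSS-10 add value, because no PSS-10-only reference model is planned

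*Protocol article*

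**What the plan says.** The primary outcome is responder status on the PSS-10. Under Data Cleaning and Preparation, "RCI for the PSS-10 before to after treatment will be computed using the following formula", "Cronbach α=0.83 from normative data will be used", and "Patients exhibiting an RCI of −1.96 will be classified as responders". The outcome is therefore a dichotomised change score with baseline PSS-10 as one of its two terms.

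The Outcomes section adds: "The PSS-10 baseline and 3-week measurement will also be used as predictors". Table 1 lists both scores among the putative predictors.

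Model Interpretation sets two aims for test-set BACC. The first is that "the model should perform better than a dummy model that simply predicts the most common responder status". The second is a BACC of at least 67%, taken as the mark of clinical usefulness. The four classifiers are also compared with one another on 5000 bootstrap samples of the test set. No reduced model is described as a reference.

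Comparison to Prior Work restates the hypothesised predictors (age, education, symptom severity, credibility, sickness absence) and then the ML aims. It says that, if these are confirmed, the findings would support the notion that "predictive models using sociodemographic, clinical, self-rated, treatment-related, and potentially cognitive variables are valuable when predicting therapy outcomes".

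**The concern.** The concluding statement credits five domains of predictors together. Part of its support is a pass on two thresholds, and neither separates those domains from the outcome scale itself. Baseline PSS-10 enters the outcome arithmetically. Week-3 PSS-10 already shows some of the change that the outcome measures. A model that used only these two scores could pass both aims, and its pass would look the same as one earned by the full battery.

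The risk is that a result driven by the early course of the PSS-10 is reported as evidence for the multimodal dataset, including the cognitive tests that Strengths and Limitations presents as a strength. A confidence interval around the 67% figure would not help, because the difficulty lies in the comparator and not in sampling error.

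**Working it through.** **The plan's own figure.** Study Design states that "300 study participants would be needed for a 90% power to detect a between-group effect size of" Cohen d = 0.4, "with a significance level of .05 and an expected attrition rate of 10"%. Taking alpha as two-sided, n per arm = 2 × (1.960 + 1.282)² / 0.4² = 131.4, so 132 per arm and 264 in total. Then 264 / 0.9 = 293.3, so 294 (296 with the t distribution). The 300 reproduces. It is the size for the two-arm comparison; the article gives no such calculation for the prediction aims.

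**The dummy.** A model that always predicts the majority class has a recall of 1 in one class and 0 in the other. Its BACC is (1 + 0) / 2 = 50% by construction.

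**The responder threshold.** The formula is not in the text at hand. The usual form is assumed: RCI = (post − pre) / (SD × √(2 × (1 − α))). With α = 0.83, the fall needed is 1.96 × √(2 × 0.17) = 1.143 SD, or about 5.7, 6.9 and 8.0 points for an SD of 5, 6 and 7.

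**Test-set size.** 30% of 300 is 90. With the 10% attrition assumed for the trial, 270 remain, which gives 189 training and 81 test patients.

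**What two PSS-10 scores can reach.** The article gives no PSS-10 SD, correlation, mean change or response rate, so all of these are assumptions. Scores at baseline, week 3 and week 12 were simulated as trivariate normal, and a logistic model was fitted on PSS-10 scores alone.

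- *Main grid, 54 scenarios.* Correlations were baseline/week 3 0.5–0.7, week 3/week 12 0.4–0.6 and baseline/week 12 0.2–0.5. The week-3 SD was 1.1 and the week-12 SD 1.0 or 1.3 times the baseline SD. The mean fall was 0.8–1.5 baseline SD (response 37–64%). With a probability cut of 0.5, baseline plus week 3 gave a large-sample BACC of 0.59 to 0.74 (AUC 0.67 to 0.83). It was at or above 0.67 in 35 of 54 scenarios (65%). Baseline alone gave 0.56 to 0.72.
- *Second grid, 81 settings* (baseline/week 3 0.5–0.7, baseline/post 0.3–0.5, week 3/post 0.45–0.65; SDs 5.5, 6.0 and 6.5). BACC was 0.61 to 0.77 at a 0.5 cut, with 70% of settings at or above 0.67. It was 0.63 to 0.77 at a cut equal to the responder share, with 78% at or above 0.67.
- *Third grid, 243 scenarios.* The range widened to 0.56–0.80, but the share reaching 0.67 was similar: 69% (0.5 cut) and 79% (cut at the responder share).
- *Finite samples.* Six scenarios were run with 189 training and 81 test patients, 1500 runs each, at a 0.5 cut. Mean test BACC was 0.65 to 0.72 with an SD of about 0.05. The chance of reaching 0.67 was 33% to 84%. The dummy's 50% was beaten in at least 99.6% of runs.

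The PSS-10-only model falls short mainly where the baseline/week-12 correlation is high and the week-12 SD is wide.

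**Planned analyses that come closest.** The ablation in Predictor Analysis belongs to the traditional regression. It removes one univariately significant predictor at a time and measures explained variance. Random forest feature importance covers one of the four classifiers. Neither gives the test-set BACC gained over the PSS-10.

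**The case against.** The strongest reply is that the concluding sentence does not rest on the ML aims alone. Its condition also covers the predictor hypotheses, and most of the listed domains map onto them: age and education, sickness absence, symptom severity, credibility. Only the cognitive domain is hedged. Those hypotheses have their own test. If baseline and week-3 PSS-10 are significant and kept, they sit in the full ablation model, so other predictors are judged beyond them. This stands, and a reader who inferred that the plan ignores incremental contribution would be wrong. But the ablation is in-sample, takes one predictor at a time and is not on the BACC scale, so it does not supply what the ML statement needs.

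It is also fair that the wording is cautious, that the self-rated domain includes the PSS-10, and that the sentence speaks of models using these variables jointly. The article does not claim that each domain adds to the PSS-10. Still, it credits all the domains from a result that could come from part of one.

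Using baseline and early scores as predictors is legitimate. The dummy and 67% aims are valid for the question whether a model predicts usefully. Neither needs to be removed.

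A reader might infer that the PSS-10 alone is bound to clear 67%. A narrow set of 18 assumed settings, cut at the responder share, does give 0.675 to 0.717 throughout. The wider grids show that this depends on the settings chosen, and the documents contain nothing that would select them.

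**Conclusion.** The point holds in a limited form. Meeting the two ML aims would show that a model predicts response. It would not show that the sociodemographic, clinical, treatment-related, cognitive or other self-rated variables contribute beyond two PSS-10 scores. Those scores alone plausibly give a BACC of roughly 0.59 to 0.77 and reach 67% in most but not all assumed settings. These figures rest wholly on assumed SDs, correlations and mean change, on the usual RCI formula scaled by the baseline SD, and on week-3 PSS-10 surviving the 20% missing-data rule. The logical gap does not depend on them: even where the PSS-10 falls short of 67%, the aims do not measure what the other domains add. This is a cheap improvement to the comparator and to one sentence of interpretation, not a flaw that invalidates the study.

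**What to change.** In Model Interpretation, add one reference model: logistic regression on baseline and week-3 PSS-10 only, fitted in the same training set and scored on the same test patients. Report each classifier's BACC minus the reference BACC, with a confidence interval for the paired difference from the 5000 bootstrap samples already planned. Keep the dummy and 67% aims.

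In Comparison to Prior Work, claim added value of the other domains from the ML results only if that interval lies above zero. If it includes zero, report that added value over the PSS-10 was not demonstrated. It would be wrong to conclude that the PSS-10 accounts for the prediction, because with about 81 to 90 test patients a real gain can easily be missed. In an illustrative simulation with 210 training and 90 test patients, the 95% interval had a half-width of about 0.09 to 0.11. A mean gain of about 0.03 was detected in 7% of runs, and one of about 0.08 in 31%.

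The cost is a two-variable model and a few lines of code. The article states that the data had not been analysed for this study as of March 2025, so on that statement the addition could still be prespecified. The downsides are an imprecise difference and possibly a less favourable conclusion.
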